## Abstract

**Background:**

Obesity is a significant contributor to breast cancer recurrence and mortality. A central mechanism by which obesity stimulates cancer progression is through chronic, low-grade inflammation in adipose tissue. Exercise interventions to target chronic inflammation has a potential to improve obesity- and breast cancer-related outcomes; however, no studies have investigated the roles of exercise in modulating adipose tissue inflammation in breast cancer survivors. Also, it is unclear which exercise prescription would be optimal to maximize the outcomes. Therefore, we designed a randomized controlled trial (Taking AIM at Breast Cancer: Targeting Adiposity and Inflammation with Movement to Improve Prognosis in Breast Cancer Survivors [AIM] Trial) to examine the mechanisms by which different modalities of exercise impact chronic inflammation as a biomarker of breast cancer prognosis.

**Methods:**

The AIM trial is a prospective, three-armed, phase II randomized controlled trial investigating the effects of a 16-week supervised circuit aerobic and resistance exercise (CARE) program versus a traditional aerobic and resistance exercise (TARE) program and attention control (AC) on adipose tissue inflammation in breast cancer survivors. 276 patients who are diagnosed with stage 0-III breast cancer, post-treatment, sedentary, and centrally obese are randomized to one of the three groups. The CARE and TARE groups participate in thrice-weekly supervised exercise sessions for 16 weeks. The AC group are offered the CARE program after the intervention period. The primary endpoint is adipose tissue inflammation assessed by core biopsy and blood draw. The secondary and tertiary endpoints are sarcopenic obesity, physical fitness and function, and patient reported outcomes. The exploratory outcomes are long-term breast cancer outcomes.

**Discussion:**

This is the first randomized controlled trial examining the effects of exercise on adipose tissue inflammation in obese, breast cancer survivors. Our findings are anticipated to contribute to a better understanding of exercise modalities and mechanisms on adipose tissue inflammation that can potentially improve breast cancer prognosis.

**Clinical Trial Registration:**

https://clinicaltrials.gov/ct2/show/NCT03091842 identifier [NCT#03091842].

## 1 Introduction

Obesity and breast cancer represent two common diseases globally with increasing prevalence worldwide (1). In the United States, 2 in 3 adults are overweight or obese and 1 in 8 women will develop breast cancer, where each independently has a profound impact on public health (2, 3). Notably, over 50% of breast cancer patients are considered overweight or have obesity (i.e., body mass index ≥ 25.0 kg/m^2^) at diagnosis, and 50-96% of them are experiencing further weight gain during cancer treatment (4–6). Moreover, obesity increases the risks of breast cancer recurrence and all-cause and cancer-specific mortality up to 40% (7, 8). A central mechanism by which obesity stimulates cancer progression is through chronic, low-grade inflammation in adipose tissue, particularly in white adipose tissue (WAT) (9–12). WAT is comprised of metabolically active adipocytes capable of secreting adipokines and proinflammatory cytokines related to tumorigeneses (9–12). Given obesity-induced inflammation in adipose tissue leading to physiological disruptions (13, 14), there is an urgent need for non-pharmacological strategies that target obesity-related inflammation to improve prognosis in breast cancer survivors.

Current recommendations by the American College of Sports Medicine (ACSM) (15, 16) encourage cancer survivors to perform a minimum of 150 minutes per week of moderate-intensity or 75 minutes per week of vigorous-intensity aerobic exercise (AE), as well as two resistance exercise (RE) sessions per week involving all major muscle groups. Considering these guidelines, AE combined with RE, referred here as “traditional aerobic and resistance exercise” (TARE), represents an effective approach to exercise prescription in breast cancer survivors, as combined programs improve systemic inflammation, metabolic diseases, and muscular strength (17–19). On the other hand, “circuit aerobic and resistance exercise” (CARE) is an innovative training program, incorporating interval and circuit training and periodization, and it has been shown to improve muscle and cardiorespiratory fitness among breast cancer survivors (20) and bone health among female cancer survivors (21). However, it is unclear which exercise program would be optimal to improve adiposity and inflammatory outcomes in breast cancer survivors.

Hence, we designed a randomized controlled trial, “Taking AIM at Breast Cancer: Targeting Adiposity and Inflammation with Movement to Improve Prognosis in Breast Cancer Survivors: the AIM trial”, as the first intervention study to compare the impact of different modalities of exercise on chronic inflammation as a biomarker of breast cancer prognosis (**Figure 1**). The primary objective of the AIM trial is to investigate the effects of CARE vs. TARE training programs on adipose tissue-driven chronic inflammation in breast cancer survivors. The secondary and tertiary objectives are to examine the intervention effects on sarcopenic obesity, physical fitness and function, cognition, and quality of life. Finally, the exploratory objective is to examine the long-term clinical outcomes. We hypothesize that CARE will reduce chronic inflammation as well as improve secondary and tertiary outcomes to a greater degree compared to TARE and attention control (AC).

**Figure 1 f1:**
[figure not shown]
Conceptual framework of the AIM trial.

## 2 Methods And Analysis

### 2.1 Study Design

The AIM study is a prospective, single-center, three-arm, phase II randomized controlled trial conducted at the Dana-Farber Cancer Institute, Boston, MA. A total of 276 breast cancer survivors with obesity and have completed chemotherapy and/or radiation are randomly assigned to one of three groups: CARE, TARE, or AC. The study involves a 16-week intervention with 4- and 8-month follow-up periods. This study protocol is in accordance with the Consolidated Standards of Reporting Trials guidelines (22), and the study schema and timeline are illustrated in **Figures 2** and **3**, respectively. This study is approved by the Institutional Review Board (IRB #20-172) and registered at ClinicalTrials.gov (NCT#03091842).

**Figure 2 f2:**
[figure not shown]
CONSORT flow diagram of the AIM trial.

**Figure 3 f3:**
[figure not shown]
Study timeline of the AIM Trial. CARE, Circuit Aerobic and Resistance Exercise; TARE, Traditional Aerobic and Resistance Exercise; AC, Attention Control. All three groups are assessed otherwise noted. Follow-up timepoints are defined as the period from the post-intervention assessments. ^*^Participants in the AC group who do not choose to perform the supplementary CARE program after the intervention period will not complete selected assessments testing at this time point. ^#^Participants in the AC group will not complete assessments at this time point.

### 2.2 Participants and Recruitment

This trial includes women with newly diagnosed stage 0-III breast cancer who have completed cancer-related treatment, and the detailed inclusion and exclusion criteria are provided in **Table 1**. Various recruitment strategies are used to identify potential participants including screening breast clinic lists, use of patient advertisements in waiting areas and through online platforms and newsletters. Once potential participants are identified through the patient list, a study coordinator contacts the patients’ treating providers or oncologists and request permission to contact the patients to invite them to participate in the study. Potentially eligible participants are further screened by study staff either in person or by phone to confirm other eligibilities, including current exercise levels using the Godin Leisure Time Questionnaire (23) and past and current medical conditions using the Physical Activity Readiness Questionnaire (PAR-Q). Interested participants are then scheduled for a visit with a member of the study staff to review the protocol and sign informed consent. Due to the ongoing COVID-19 pandemic, we have also adopted the use of electronic consent (e-consent) to obtain consent remotely.

**Table 1 T1:** Inclusion and exclusion criteria of the AIM Trial.

Inclusion Criteria	Exclusion Criteria
• Over 18 years of age • Newly diagnosed women with stage 0-III breast cancer, low grade disease positive for estrogen and progesterone receptors • Having undergone lumpectomy or mastectomy, (neo)adjuvant chemotherapy and/or radiation therapy • Not receiving concurrent cancer treatment • Centrally obese with the following criteria: BMI >30 kg/m^2^ or body fat >30% (as measured by bioimpedance analysis), waist circumference >35 inches • Currently participating in less than 60 minutes of structured exercise per week • Without any cardiovascular, respiratory, or musculoskeletal disease or joint problems that preclude exercise • Not currently or planning to become pregnant • Speaking English	• Metastatic disease or other active malignancies • Currently receiving any other investigational agents, or concurrent biological, chemotherapy, or radiation therapy • Not completed any of breast cancer treatment (e.g., surgery, chemotherapy, or radiation) • Having uncontrolled illness including ongoing or active infection, uncontrolled diabetes, hypertension, or thyroid disease that preclude participation in exercise • Participates in more than 60 minutes of structured exercise/week • Is planning reconstructive surgery with flap repair during trial and follow-up period • Smoker • Unable to travel to research facilities

### 2.3 Randomization and Blinding

Upon the completion of baseline assessments, patients are randomly assigned to either CARE, TARE, or AC in an equal allocation ratio (1:1:1) using a permuted-block design with varying block sizes. The randomization is stratified by menopausal status (premenopausal and postmenopausal) which is evaluated at time of diagnosis. A study biostatistician ([name]) prepares the randomization schema prior to trial start-up, and the randomization allocation is provided to staff *via* a web-based application (REDCap) (24), and study investigators are blinded to the randomization process. The intervention allocation is not blinded to the study participants, interventionists, and outcome assessors due to the nature of exercise intervention.

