### 2.8 Sample Size

We anticipate recruiting 276 patients over a 48-month period and randomizing 92 patients to each arm of the study. Our hypotheses and analyses regarding our primary and secondary outcomes will reflect the comparison between CARE vs. TARE, and CARE vs. AC. Since the primary analysis involves two statistical comparisons, we will apply Bonferroni adjustment to control the overall type I error rate at 0.05 level. We estimated samples sizes for these two comparisons with each evaluated at two-sided alpha = 0.025. Our estimates of exercise intervention effect sizes were derived from randomized clinical trials (78–80) in addition to our preliminary data (81); most significantly, a study comparison of traditional endurance training vs. high-intensity circuit training (80) with effect sizes for outcomes common to our proposed trial (fat mass, lean body mass) was approximately 0.5-0.6. Effect sizes comparing exercise interventions to AC groups were larger, on 0.7-1.0. Our preliminary data compared exercise to AC (15 subjects per group), effect sizes were on the order of 1.0 (body composition measures) to 2.5-3.0 (inflammatory and other biomarkers) (81). The sample size determination was based on the comparison of the primary outcome between the CARE and TARE group because we expected that the difference between the CARE and AC group was larger than that between the CARE and TARE groups. We used an effect size of 0.5, two-sided alpha=0.025, and 80% power to estimate the sample size for comparisons of CARE vs. TARE, yielding a required 78 participants per group. To account for an anticipated 15% dropout rate, we will randomly assign 92 participants to each of the three groups. This will provide 80% or higher power to detect effect sizes of 0.5 and higher for other outcomes. For the optional biopsies, the sample size has been estimated at 50 participants per group based on our preliminary work (81). This will provide 80% power to detect a between-group difference, at a two-sided 0.025 alpha level, when the effect size is 0.9 for biopsy outcomes.

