### 2.9 Statistical Analysis

Initial descriptive analyses will be used to evaluate baseline comparability among the three intervention groups, using ANOVA, or Kruskal-Wallis tests for continuous variables and chi-square tests for categorical variables. Unless otherwise specified, Statistical testing will be conducted at a two-sided 0.05 alpha level to determine statistical significance. For our primary and secondary outcomes, the variables used for the primary analysis will be the 2- and 4-month measurements of trial outcomes assessed during and at the end of the intervention period. Linear mixed-effects models will be used with the longitudinal data for the between-group comparisons, where two indicator variables for the treatment group (TARE, AC) relative to CARE, the baseline value of the outcome, and an indicator variable for measurement time (2-month/4-month) will be included as fixed-effects and subjects as random-effects in the models. With Bonferroni correction applied, the Wald test will be performed at 0.025 two-sided alpha level for each of the two comparisons regarding treatment effects (i.e., CARE vs. TARE, and CARE vs. AC); the between-group differences will be reported with corresponding 0.975 two-sided confidence intervals. Significant group differences will be followed by stratified analyses within measurement time (two and four months), and testing of group-time interactions, to evaluate treatment group differences within measurement time.

Post-intervention outcomes will be evaluated using the same linear mixed-effects models. The dependent variables will be the 8- and 12-month post-intervention measures, with the 4-month post-intervention measure, included as a fixed-effect.

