The primary analysis would include all completed outcome assessments (regardless of whether the woman stayed on the intervention), inviting those who drop from the intervention to return for outcome assessments. The only missing data here would be those who drop the intervention and do not return for outcome assessments. Preliminary analyses will compare women who do and do not contribute to this analysis on baseline characteristics. Sensitivity/subgroup analyses will include (1): the receipt of chemotherapy as an established a-priori confounding factor due to possible chemotherapy-induced changes of chronic inflammation in adipose tissue (82–85), (2) multiple imputations of missing 2- and 4-month data (to evaluate the effect of missing data) (3); additional adjustment for baseline variables that differ between groups (to evaluate the effect of possible group differences on variables related to outcomes); and (4) adherence-based analysis, limiting subjects to those with at least 80% adherence (to estimate treatment effects under full adherence).

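### The mixed models of section 2.9 leave out menopausal status, the randomisation stratification factor; this can make the tests conservative and forgo a small amount of power

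*Protocol article*

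**What the plan says.** Section 2.3 (Randomization and Blinding) assigns women to CARE, TARE or AC "in an equal allocation ratio (1:1:1) using a permuted-block design with varying block sizes". It names one stratification factor: "The randomization is stratified by menopausal status (premenopausal and postmenopausal) which is evaluated at time of diagnosis".

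Section 2.9 (Statistical Analysis) specifies the model for the primary and secondary outcomes: "two indicator variables for the treatment group (TARE, AC) relative to CARE, the baseline value of the outcome, and an indicator variable for measurement time" (2 or 4 months) "will be included as fixed-effects and subjects as random-effects in the models". The follow-up outcomes use the same type of model, with the 4-month value as the covariate. Menopausal status appears in neither.

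The sensitivity and subgroup analyses in section 2.9 cover receipt of chemotherapy, multiple imputation, "additional adjustment for baseline variables that differ between groups", and an analysis of adherent women. None names menopausal status.

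Section 2.8 (Sample Size) sizes the trial without reference to covariates: "We used an effect size of 0.5, two-sided alpha=0.025, and 80% power to estimate the sample size for comparisons of CARE vs. TARE". The result is 78 per group, raised to 92 for 15% dropout. Biopsies are optional, with 50 per group planned.

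**The concern.** Stratified blocks hold menopausal status nearly equal across arms. If the factor is prognostic, the treatment contrast then varies less from one randomisation to another than it would under simple randomisation. A model without the factor leaves its contribution in the residual variance and reports the larger standard error. Intervals come out too wide and the test rejects a true null less often than its nominal level.

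The listed sensitivity analyses would rarely repair this. Adjustment is triggered by a difference between groups, and stratification makes such a difference unlikely for this variable. The loss also has nothing to do with imbalance: it arises when the factor is balanced and prognostic.

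At stake is some precision in the CARE versus TARE and CARE versus AC comparisons, and a covariate set that does not follow the design. Adding the factor after outcomes have been seen would be open to the charge of a post hoc choice.

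**Working it through.** **Inputs.** From section 2.8: effect size d = 0.5, two-sided alpha 0.025 per comparison, 80% power, 78 evaluable and 92 randomised per group, and 50 per group with d = 0.9 for biopsy outcomes. Assumed, because the document gives no value: R², the share of outcome variance left after baseline adjustment that menopausal status explains.

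**The plan's own figure.** By the normal approximation, n = 2(2.2414 + 0.8416)²/0.5² = 76.04, so 77. The two-sample t-test gives 77.3, so 78. Dropout: 78/0.85 = 91.8, so 92, and 3 × 92 = 276. The stated figures reproduce, from an unadjusted two-sample comparison.

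**Effect of leaving the factor out.** Take the SD seen by the model without the factor as 1.

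- Model-based SE = √(2/78) = 0.1601.
- True SE under stratification = 0.1601 × √(1 − R²).
- Overstatement of the SE = 1/√(1 − R²) − 1.
- Actual size = 2[1 − Φ(2.2414/√(1 − R²))].
- Power, factor omitted = Φ((0.5 − 2.2414 × 0.1601)/true SE).
- Power, factor included = Φ(0.5/true SE − 2.2414).

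At R² = 10%: true SE = 0.1519; size = 2[1 − Φ(2.363)] = 0.0181; power omitted = Φ(0.1411/0.1519) = Φ(0.929) = 82.4%; power included = Φ(3.291 − 2.241) = Φ(1.050) = 85.3%.

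| Assumed R² | SE overstated by | Actual size | Power, omitted | Power, included |
|---|---|---|---|---|
| 0% | 0% | 0.0250 | 81.1% | 81.1% |
| 1% | 0.5% | 0.0243 | 81.2% | 81.5% |
| 2% | 1.0% | 0.0236 | 81.3% | 81.9% |
| 5% | 2.6% | 0.0215 | 81.7% | 83.2% |
| 10% | 5.4% | 0.0181 | 82.4% | 85.3% |

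**Simulation check.** Three arms of 78 were drawn with stratified permuted blocks, a baseline covariate, one outcome per woman, 30% in one stratum (assumed), and 6,000 runs per setting. A difference of D residual SDs between strata gives R² = 0.21D²/(1 + 0.21D²). Here the 0.5 effect is in residual SDs, the scale left after the factor is removed.

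| D | R² | Mean model SE, omitted | Power, omitted | Power, included |
|---|---|---|---|---|
| 0.3 | 1.9% | 0.162 | 80.2% | 80.9% |
| 0.5 | 5.0% | 0.165 | 79.4% | 80.9% |
| 0.8 | 11.9% | 0.171 | 76.9% | 80.9% |

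The true SE is about 0.160 throughout. At D = 0.8 with no treatment effect, the rejection rate without the factor was 0.017. The direction agrees with the formulas.

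**Biopsy outcomes.** At 50 per group and d = 0.9, t-test power is about 98.6%, so the power at issue is negligible if that effect size is right. (Section 2.8 states 80% here; that mismatch is a separate matter.) If the tissue effect were nearer 0.62, where 50 per group gives 80%, the loss would resemble the 78-per-group case.

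**The case against.** The strongest reply is that nothing stated in the plan is wrong. The 78 per group was derived without this covariate and reproduces. Leaving the factor out cannot produce false positives. The baseline value of the outcome is already in the model and will absorb stable differences between pre- and postmenopausal women, so only a residual association counts, and it could be nil. Status is recorded at diagnosis while women enrol after treatment, so the stratum may be out of date by baseline, which weakens the association further. For the M1/M2 tissue outcomes, power at the planned effect size is near 99% either way. All of this stands, and it limits the size of the point.

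It can also be said that this is a condensed article and that a statistical analysis plan may add the factor. That lowers confidence somewhat. But section 2.9 gives the model term by term and names other adjustments, so the text as written departs from the design.

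Stronger readings that a reader might infer are not supported:

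- *The standard errors are certainly too large.* This needs a residual association that the document does not quantify.
- *The trial is underpowered.* In the formulas, power without the factor stays at or above 81%. It falls below 80% in the simulation only because the 0.5 is scaled to the residual SD, and section 2.8 does not say which SD it means.
- *The investigators stratified because they expect menopausal status to be prognostic for these outcomes.* Section 2.3 gives no reason.
- *Stratification rules out imbalance.* It makes imbalance unlikely among all women randomised. It does not guarantee balance among biopsy volunteers or among those left after dropout. There the listed adjustment might be triggered, but only by a data-dependent rule and only in a sensitivity analysis.

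**Conclusion.** The point holds in a limited form: the randomisation uses a factor that the stated models leave out. If menopausal status predicts the 2- and 4-month outcomes beyond baseline, the standard errors are somewhat too large and the 0.025 tests conservative. For an assumed residual R² of 0% to 10%, the overstatement is 0% to 5.4% and the forgone power about 0 to 3 points at 78 per group, with the 0.5 effect scaled to the SD that includes the factor's contribution. The planned 78 and 92 per group stand and type I error is not inflated.

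The gain from adjusting is probably small. In the voluntary biopsy subset the reason to adjust is protection against imbalance rather than power. The change is worth making because it is almost free and aligns the analysis with the design.

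**What to change.** In section 2.9, add menopausal status as a fixed effect to the primary, secondary and follow-up mixed models. Use the stratum recorded for randomisation (status at diagnosis), not a later reassessment. State this before outcomes are examined, and keep any statistical analysis plan consistent with it.

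The cost is one extra term and one degree of freedom. No new data are needed, since the variable is known for every woman randomised, and the sample size does not change.

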### 2.4 Exercise Intervention

The CARE and TARE groups receive a 4-month exercise intervention at an exercise facility located within the cancer center, and all exercise sessions are supervised one-on-one by a clinical exercise trainer. Both exercise programs consist of a total of 48 sessions, provided three times per week for 16 weeks for approximately 60 minutes per session. Heart rate (HR) is monitored throughout all training sessions using a Polar^®^ heart monitor (Lake Success, NY). Each session begins with a 5-minute warm-up of low-intensity AE and concludes with 5 minutes of the same 3-4 static stretches conducted by the AC group, which will target major muscle groups, each held for 30 seconds. One-repetition maximum (RM) and peak oxygen consumption (VO_2peak_) obtained during baseline testing are used to determine resistance load for each exercise and aerobic intensity, respectively. The details of a single exercise session of each CARE and TARE program are illustrated in **Figure 4**.

